### Analysis

Qualitative data will be recorded, anonymous, integrally transcribed and imported into NVivo12 software to achieve thematic and semantic content analyses, using analyses of similarity and correspondence factorial analyses. Two analytic team members will independently code the initial interview for each participant interviewed to clarify meanings of codes and come to consensus when disagreements occur, thus defining the initial code book [40]. The construction process of these thematic categories, coding, is both inductive and deductive because the development of themes and sub themes rests on both literature and emerging categories of empirical analysis. Qualitative analysis could draw a typology of the various cancer care coordination professions’ representations.

Quantitative data will consist in describing contextual factors as organisational contexts, clinical contexts, social contexts … and analysing associations between contextual factors and either satisfaction regards to care coordination for patients, caregivers and referral professionals, or quality of life at work (for cancer care coordinator nurses). Quantitative variables will be described in terms of numbers, percentages, and 95% confidence intervals according to the exact binomial distribution. Comparisons will be made by the Chi-square, corrected Chi-square or exact Fisher test. A logistic or polytomial regression model is used to take into account the adjustment variables. The quantitative variables will be described in terms of mean, standard deviation, median, extent and interquartile range. Comparisons will be made by Student test, Student test for unequal variances, Wilcoxon test, according to the distribution of the variable of interest.

Mixed-methods analysis: The both qualitative and quantitative analyses will be performed simultaneously over the same period of time (two concomitant analyses). Then, some results obtained in the qualitative analysis could be quantified and introduced into the final quantitative analysis. At last, qualitative and quantitative methods will be combined in a convergent interactive analytic design (data triangulation) to examine interdependencies between reference framework and observed elements. All data will be analysed according to the theoretical reference framework with the ability to allow new themes emerging from the data to be identified. This approach is a combination of deduction using the theoretical framework and induction to identify insights emerging from the data. The development of this new operational model will result in a comparative analysis between observed practices and a theoretical model.

### Monitoring and coordination

The Steering and scientific committees of EPOCK include oncologists, epidemiologists, researchers on management and organisation sciences and health psychology.

The EPOCK’s interdisciplinary research team was assembled because of its experience and expertise in evaluating complex interventions (expertise in qualitative and quantitative research methods, appropriate interdisciplinary theoretical expertise) [50].

The Epock study is ongoing. Investigators are still collecting data.

## Discussion

### Expected results

This paper presents a new protocol aiming at evaluating cancer care coordination interventions through a new model by comparing a theoretical reference framework of care coordination with practices in oncology within the French Healthcare system.

The Epock project aims to address the lack of information on coordination of care in France by three main outputs:Building a theoretical reference framework for care coordination in France

The EPOCK Phase 1 will identify key elements contained in a reference framework for care coordination interventions in any clinical situation (multiple chronic conditions, physical or mental and long-term care patients). This reference framework will help the Epock research group to build in part the qualitative study tools needed in the second step of the Epock study (observation and interviews guides), and to analyse the practices of care coordination nurses in the specific context of oncology in France. It could also be useful in other clinical contexts and could help to compare care coordination programs in various contexts; to develop position profiles and job description for care coordination workers and to develop criteria for evaluating best practices among care coordination professionals and work environment. It could be used to build a wide range of teaching materials and training programs from under-graduate to post-graduate programs and lifelong learning courses. It could also be used by decision makers in order to develop care coordination evidence-based clinical indicators.2)Analysing in fine details practices and contexts of the reality of nursing coordination professions in France

This mixed-methods analyses will allow us to define relevant components of cancer care coordination interventions within the context of the French health care system: a) Structural dimension of the coordination intervention (organisational rules, human, financial, material, symbolic resources, representations, beliefs); b) Actors of coordination: roles, competences, their interactions with the other healthcare stakeholders, their qualifications (competence grid on knowledge, know-how); c) Process of care coordination: collection of the nature of the coordination tasks associated with the workstation (types of care, types of practices, types of activities) and their purposes (purpose and objective of coordination), with the possibility of modelling the process and the expected results of this coordination; d) Environment and context of coordination: clinical, organisational and managerial contexts with which these coordination professions interact.

The immediate expected outcome of the Epock study will be to provide information to define roles and duties, requirements and optimal care contexts of the coordination nursing professions and thus could contribute to harmonising practices for this profession.3)Designing an operational model consisting of recommendations that will help to align the profession of cancer care nurse-coordinator with the theoretical reference framework

This study will result in an evaluation framework identifying key model elements, barriers, and facilitators that can be used to guide cancer care coordination interventions in the French healthcare system in the absence of a systematic and uniform referral system for cancer care coordination intervention. The EPOCK study will further our knowledge of the process of cancer care coordination intervention. This could allow us to accurately define the elements of nurse intervention processes and their alignment with the theoretical model (what nurses do, what they should do …) and thus draw up an operational model for the coordination of cancer care in France that could be useful in many purposes:Contribution to practices in oncology: it would help to describe and implement programs of cancer care coordination intervention, to harmonise practices (with job profile description for cancer coordination nurses), to assist public decision-makers to identify the optimal targets, profiles and scope of action for cancer coordination professionsImplications for teaching and education: there is currently an increasing number of training courses in France on the coordination of cancer care, but none are theory-based. It would be appropriate to develop a dedicated university degree for cancer coordination nurses based on the reference framework and the nursing profession profile found in the Epock project.Implications for the management and organisation of cancer care: comparing programs for cancer care coordination by developing evaluation criteria of care coordination nurses best practices; for decision makers in order to develop cancer care coordination evidence-based clinical indicatorsImplications for research: it should produce key elements for cancer care coordination intervention effective implementations and for designing further medico-economic evaluation of cancer care coordination intervention impact

### Strengths and limitations

Process evaluation of complex interventions usually requires a combination of quantitative and qualitative methods in order to provide a broader perspective. There is a strong need for a theoretical model of care coordination to provide a reference framework against which to observe cancer care coordination practices in France. This theoretical model will help the Epock research team to determine care coordination framework dimensions that will be later appropriate for scaled survey questions (quantitative analysis) and interview questions (qualitative analysis). In order to build this theoretical model we will use an inductive process conducted iteratively using a review and a structured consensus method. The international systematic review on the impact of care coordination interventions will be carried out to fully describe all dimensions and detailed elements which can be included in this reference framework. The search will be as wide as possible to collect a very large and comprehensive description of care coordination interventions related to the contexts, activities, actors, tools and impact of this complex intervention. As the term “care coordination” is not part of the MeSH (Medical Subject Headings) terms, care coordination is often approached by combinations of other terms such as “comprehensive care”, “case management”, “care integration” or “continuity of care”, “coordinated care” or “integrated care”. However, these terms are not specific to care coordination and will not answer our research question. In addition, these terms further confuse the definition of care coordination. To avoid making any a priori assumptions about the definition of care coordination, we have chosen, for the research equation, to include only terms that specifically contain the word “coordination” or “coordinated”. The review team will include at least one person with methodological expertise in conducting systematic reviews and one expert of knowledge. We will limit the search to the period from the early 1990s onwards and this will enable us to identify all but the very small minority of systematic reviews conducted before then [46].

We choose a nominal group technique to provide group dynamics by direct interactions between experts, and structure a consensus by giving equal weight to each participant. The nominal group technique accompanied by multi-voting technique is a well-established, structured, multistep, facilitated, group meeting technique used to generate a consensus and prioritise relevant elements [41, 47]. We will ensure that all stakeholders are represented, including patients as experts [52].

Qualitative studies are methods promoted in the field of complex interventions to refine analysis of “care coordination processes”. In general, the choice of a qualitative method is appropriate for a comprehensive perspective of a given phenomenon, which is, here, to describe and analyse the “why” and “how” of cancer care coordination, in its ‘natural’ (in field contexts) context. The coordination of cancer care is sufficiently innovative or not yet stabilised to justify its use. The qualitative study design follows the COREQ checklist [68]. Objectivity of qualitative methods is based on triangulation of information sources (observations, interviews and focus groups). Triangulating such data strengthens validity and will help to analyse all stakeholders’ representations, perceptions and satisfaction with cancer care coordination. These data will present an in-depth examination of the role of health professionals in coordinating cancer care, their related professionals and also patients and caregivers’ priorities and preferences. This qualitative approach will be complemented by a quantitative analysis.

Quantitative methods (by questionnaires) are appropriate insofar as they seek to quantify, explain and predict a phenomenon that is sufficiently known and for which content to be measured is relatively stable or standardised. Results of these standardised scales should highlight the main organisational characteristics of the coordination nursing professions and link them to their attitudinal effects, taking into account the main psychosocial risks currently associated with the quality of life at work and the effectiveness of nurses’ work. These measures are an important component to the study, which aims to understand and describe these new professions in their entirety. All the selected scales are validated and used regardless of organisational or cultural contexts. The majority of them have been used previously by researchers in French healthcare system and have been validated in French.

For professionals working with coordination professionals, as well as the patients and their caregivers that we will follow, we plan to add a measure of coordination satisfaction and management by a short questionnaire designed ad hoc, in the absence of an established measurement scale.

The added value of the quantitative approach is primarily to capture the psychosocial perceptions of coordination professionals regarding their work environment and quality of life at work. We hypothesise that perceived organisational support and role tensions (conflict and ambiguity) could influence their level of performance and involvement in their role. These quantifiable elements, which have already been studied in the managerial and psychosocial literature in other contexts [69], contribute to the exploration of coordination nurse professions. Despite the heterogeneity of coordination practices, these results will highlight the psychosocial effects induced by these new professions and will make it possible to identify levers for organisational and managerial action.

Quantitative analyses will be complemented by qualitative analyses in order to identify potential factors associated with the quality of life at work or patients’ quality of life. Quantitative analyses will explore the relationships between the different variables measured: relations between perception of the work context (organisational support, role tension), sense of personal effectiveness, quality of work life and patients’ quality of life. Finally, principal component analysis and hierarchical clustering analysis will be conducted to identify typologies based on pre-analyses items already found in both qualitative and quantitative analysis.

The process of theorising is enhanced when qualitative and quantitative methods are mixed and inductive and deductive processes are combined [70, 71]. During Epock phase 1 (inductive methods), application of inductive methods will involve reviewing the empirical data that emerged from the overview of reviews. Variables identified in the consensus group will define care coordination intervention reference framework. During Epock phase 2 (deductive and inductive methods), we will use a combination of deduction using the theoretical framework already found in phase 1 and induction to identify insights emerging from the observed data [72]. Results from phase 2 will list components of the operational cancer care coordination model and their links with the theoretical framework [73]. This could lead to recommendations on the content of the model (process, job profile, skills …). Mixed-methods provide a high potential for such a modellisation [74].

Mixed-method strategies can offset both inductive and deductive analysis weaknesses by allowing for both exploration and analysis in the same study. Combining methodologies helps to reduce the personal biases of the researcher.

### Justification of study population

In order to capture the heterogeneity of the cancer coordination nursing professions and the diversity of contexts, we chose a national multicentre study targeting all categories of health care institutions (according to their status and size) in which these professions have been set up. The 10 centres included in Epock study are geographically spread in five French regions on the whole French territory and have both rural and urban areas. They represent the geographical diversity of the French territory practices. The choice to focus the study solely in health facilities and nurse functions is justified by the concern to make the measure more reliable by referring to relatively identical work contexts (health care institutions) and professions with a common set of skills (nurses). In addition, nurses are the main workforce in the cancer care coordination professions in France and they represent a new profession to be evaluated. One of the limitations of our study is that we do not have the whole diversity of nursing occupations in each selected health care facility. However, it was important to reduce the scope of the project in terms of feasibility with regard to the sample size (1200 cases observed) and timing of the project (36 months planned).

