**Discussion:**

This study will result in an evaluation framework identifying key models and key elements relative to cancer care coordination interventions that can be used to guide management of cancer care coordination nursing occupations within the French healthcare system. EPOCK would also assist in public decision-making to identify optimal targets, skills profiles and scope of actions for cancer coordination professions. Finally, EPOCK will describe typology of nurse practices in cancer care coordination and thus obtain precise preliminary information essential for drafting a medico-economic evaluation study of these new nursing professions’ impact.

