#### Phase 2: description of practices, contexts, perceptions and attitudes related to care coordination occupations by nurses in oncology (Table 2)

##### Population

The study population encompasses all nurses with a hospital-to-city coordination activity for cancer patients, EPOCK target nurses, and the professionals, patients and caregivers with whom they interact as part of their coordination activity. In order to capture the heterogeneity of the cancer coordination nursing professions and the diversity of contexts, we will consider all the categories of health care institutions, according to their status and size, in which these nurses have been implemented.

Study population combines the following different individuals and structures (Table 2). The identification of the different types of nursing professions leads us to select the centres where they have been implemented:**Target nurses**: Seven different subtypes of cancer care coordination nurses, with different designations, were identified and will be referred to as “target nurses” in the remainder of this paper. Target nurses designations were identified through publications in the literature (French or international papers published by French research teams) and by collecting operational feedback from French cancer professionals network experiencing cancer coordination nursing national program and expert opinion.The “**IDEC**” (IDEC “*Infirmier Diplomé d’Etat de coordination en Cancérologie*”) are cancer coordination nurses who were first implemented in France.The “**IDE DA/TAS**” nurses (“***I****nfirmier du*
***D****ispositif d’****A****nnonce ou*
***T****emps d’****A****ccompagnement*
***S****oignant*”) responsible for the support of delivering breaking bad news (nursing support for diagnosis announcement procedure) and for assessing supportive cancer care needs,The “**IPO**” nurse (“***I****nfirmier*
***P****ivot en*
***O****ncologie*”) based on the Canadian model [43, 53, 54],The “**AMA”** nurses (“***A****ssistance*
***M****alades*
***A****mbulatoires”)* for ambulatory patient support in hematologic cancers-related patients [42, 55, 56],The “**COACH”** (“*infirmier*
***CO****ordination*
***A****ssistance*
***CH****imiothérapie*”) nurse telephone support at home during chemotherapy [46],The “**IDECO”** (“***I****nfirmier spécialisés en*
***C****himiothérapie*

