***O****rale”)* specialised nurses in oral chemotherapy,The “**IDE HAD-CAD”**
*(“****I****nfirmier coordonnateur d’****H****ospitalisation*
***A D****omicile pour les*
***C****himiothérapies*
***A D****omicile”)* coordinating nurse specialised in Hospital Care at Home for intravenous chemotherapy at home.**Centres.** We select all types of health care facilities existing in France: university or non-university centres, public or private, comprehensive cancer centres, and hospital care at home (HAD), in urban or rural areas, regardless of their size (large, medium and small centres). A total of ten centres were selected from five French regions because each of them has implemented a subtype of target cancer coordination nurse (Table 1). We will thus exclude: the PTAs (integrated platform for professionals facilitating patient’s orientation and professional’s coordination) that have been recently designed at a national level and implanted at a local level because they don’t coordinate from the hospital to the city, the healthcare and social service networks, private home-based care providers and healthcare houses.**Non-target cancer coordination nurses**. They will be identified by each centre in addition to the target nurses. They represent all the coordination nurses implemented in each selected centre. Won’t be involved other professions of cancer coordinators: coordinating medical doctors from care networks, coordinating medical doctors from hospital care at home, practitioners from centres for cancer care coordination (the French 3Cs), practitioners from French regional cancer networks. Nevertheless, these coordinators will be included as “referral professionals” to cancer coordination nurses (target and non-target).“**Referral professionals”** to cancer coordination nurses working inside the selected centre (hospital professionals: medical [oncologists, radiotherapists, surgeons]; paramedical [nurses, health officers], administrative [medical secretary, medical-administrative assistant], supportive oncological care [social worker, psychologist, dietician, physiotherapist ...], patient associations…) and outside (primary care providers and home care workers) who have activities related to cancer coordination nurses. They will be identified by target and non-target nurses.**Patients** with a pathway coordinated by a target nurse: adult patients with any types of cancer at any stages, who have been coordinated in the last month or have had at least 2 contacts with the cancer care coordinator nurse (patient-cancer care coordinator nurse pairs). Patients will be selected by target and non-target nurses already included in the Epock study (5 patients per coordination nurses).**Caregivers** chosen by patients already selected (patient-caregiver pairs): one caregiver per patient. If the patient is isolated, no relatives will be included.

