
**Table 1 Tab1:** Epock project population: Selected target nurses and centres

N°	Target nurses	Target centres	Target territories	City	MSO size	Status of Health facilities
1	IDEC	University public hospital (extra-large size)	Region 1	Bordeaux	T5	Public
		Community public hospital (medium size)	Region 1	Libourne	T3	Public
		Private clinic (medium size)	Region 1	Bordeaux	T3	Private
2	IDEDA /TAS	Community public hospital (small size)	Region 1	Langon	T2	Public
		Private clinic (small size)	Region 2	Avignon	T1	Private
3	IPO	University public hospital (small size)	Region 3	St-Priest-En-Jarez	T1	Public
4	AMA	University public hospital (extra-large size)	Region 4	Toulouse	T5	Public
5	COACH	Comprehensive cancer centre (medium size)	Region 4	Toulouse	T2	private health institution with public interest
6	IDECO	Comprehensive cancer centre (medium size)	Region 5	Paris	T3	private health institution with public interest
7	IDE HAD CAD	Hospital care at home establishment (medium size)	Région 1	Talence	T3	private health institution with public interest
total	7 subtypes	10 centres	5 regions	8 cities	4 sizes	3 status

Region1: Nouvelle Aquitaine; region 2: Provence-Alpes-Côte d’Azur ; region 3: Auvergne-Rhône-Alpes ; region 4: Occitanie ; region 5: Ile-De-France

MSO size: Medicine, Surgery and Obstetrics size based on RSA (standardised discharge summaries) T1: [30 ; 6600 [ ; T2: RSA activity [6600 ; + 15000 [ ; T3: RSA activity [15000 ; + 40400 [ ; T4: RSA activity [40400 ; 90000 [ ; T5: RSA activity [90000 ; + infinity]

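### Five of the seven target nurse subtypes occur in one centre only, so quantitative contrasts between subtypes cannot be separated from single-centre effects

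*Protocol article*

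**What the plan says.** All references are to the protocol article.

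- **Population.** "Seven different subtypes of cancer care coordination nurses, with different designations, were identified". On site selection: "A total of ten centres were selected from five French regions because each of them has implemented a subtype of target cancer coordination nurse", that is, selection was by subtype.
- **Table 1.** IDEC is in three centres and IDE DA/TAS in two. IPO, AMA, COACH, IDECO and IDE HAD-CAD are in one each. The table totals are 7 subtypes, 10 centres, 5 regions, 4 sizes and 3 statuses.
- **Analysis.** Contextual factors, with organisational context named first, are to be related to satisfaction (patients, caregivers, related professionals) or to nurses' quality of life at work. The tests named are Chi-square, Fisher, Student and Wilcoxon, and "A logistic or polytomial regression model is used to take into account the adjustment variables". The adjustment variables are not listed and no centre term is mentioned.
- **Abstract (Discussion) and Expected results.** The study should help decision-makers to "identify optimal targets, skills profiles and scope of actions for cancer coordination professions".
- **Justification of study population.** The stated limitation is that "we do not have the whole diversity of nursing occupations in each selected health care facility", defended on grounds of feasibility.

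**The concern.** Where a subtype exists in one centre, the subtype and the institution are the same variable. A difference in satisfaction between, say, IPO and AMA patients could come from the nursing role, the hospital's size, its region, its case mix or its staff. More patients per nurse cannot resolve this, because none of the extra patients comes from a second centre with that role.

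The tests named in Analysis treat respondents as independent. Applied to a factor that is constant within a centre, they count patients as replicates of the factor when the replicates are centres. The resulting p-value would look like evidence about the role. The results are meant to inform job profiles and public decisions, so a single-centre difference could be read as a property of a nursing profession.

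**Working it through.** **1. The article's own figures.** Counting distinct levels in Table 1 reproduces its totals: 7 subtypes, 10 centres, 5 regions, 4 sizes (T1, T2, T3, T5) and 3 statuses. The centres per region are 5, 1, 1, 2 and 1 for Regions 1 to 5. The questionnaire total also reproduces: 38 + 380 + 190 + 190 = 798.

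**2. Rank of centre-level models.** Each centre is one row, dummy-coded from Table 1. Parameters = 1 + the sum of (levels − 1). For all four factors this is 1 + 6 + 3 + 2 + 4 = 16.

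| Factors in the model | Parameters | Rank | Residual centre df (10 − rank) |
|---|---|---|---|
| subtype + size | 10 | 9 | 1 |
| subtype + status | 9 | 8 | 2 |
| subtype + region | 11 | 8 | 2 |
| subtype + size + status | 12 | 10 | 0 |
| subtype + size + status + region | 16 | 10 | 0 |
| size + status | 6 | 6 | 4 |
| status + region | 7 | 7 | 3 |
| size + region | 8 | 7 | 3 |
| size + status + region | 10 | 9 | 1 |

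Every model that combines subtype with another factor is rank-deficient. Among the models without subtype, size + status and status + region are full rank, and the other two fall short by one.

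**3. Estimable pairwise contrasts in the four-factor model.** Subtype 0 of 21; region 0 of 10; size 1 of 6 (T3 against T5); status 1 of 3 (private against public). With subtype and one other factor, the estimable subtype contrasts are 9 of 21 (size), 9 of 21 (status) and 4 of 21 (region). Using the printed size labels instead of the T codes leaves the four-factor rank at 10, of 15 parameters.

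**4. Type I error of a t test between two single-centre subtypes.** With n patients per centre and intraclass correlation ρ, the true variance of the mean difference exceeds the variance the test assumes by the factor

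k = (1 + (n − 1)ρ) / (1 − ρ),

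and the two-sided error at nominal 5% is about 2[1 − Φ(1.96/√k)]. The article gives no ρ; 0.05 and 0.10 are assumptions.

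- n = 5 (five patients per coordination nurse, one target nurse per centre):
  - ρ = 0.05: k = 1.20/0.95 = 1.263, error 8.1%.
  - ρ = 0.10: k = 1.40/0.90 = 1.556, error 11.6%.
- n = 19 (190 patients / 10 centres, assuming equal centres and that every nurse in a centre counts as its target subtype):
  - ρ = 0.05: k = 1.90/0.95 = 2.00, error 16.6%.
  - ρ = 0.10: k = 2.80/0.90 = 3.111, error 26.7%.

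These use the normal approximation. With t quantiles on 2n − 2 degrees of freedom in place of 1.96 and Φ, the errors are 7.4% and 10.2% for n = 5, and 16.0% and 25.8% for n = 19. At ρ = 0.01 the normal formula gives 5.6% (n = 5) and 7.3% (n = 19), so a very small centre effect would do little harm.

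**5. Non-target nurses.** They are 28 of the 38 surveyed nurses (74%), in the same ten centres, and their types are not tabulated. If all of them share their centre's target subtype, 0 of 21 subtype contrasts are estimable once centre is in the model. If every centre also has a nurse of one common type, all 21 become estimable, provided centre effects are additive. The article does not show which case is nearer.

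**The case against.** - **No subtype test is written down.** Analysis speaks of contextual factors and unnamed adjustment variables, so the four-factor model is an illustration and not the authors' plan. A condensed article may also leave covariates and the handling of centre to a fuller document, and their absence is not the point here. This stands. The sampling frame, however, is fixed in Table 1, and no analysis plan can recover contrasts that the ten centres do not contain.
- **Much of the context is measured per person.** Perceived organisational support and role conflict and ambiguity are scored by each nurse, and Strengths and limitations calls such perceptions the main added value of the quantitative part. They vary within centres, so their associations are not aliased with centre by design. This stands in full.
- **Non-target nurses may supply overlap.** The section on semi-structured interviews says the nurses included cover the different types in the centres studied. Overlap across centres is neither shown nor excluded.
- **The claims are hedged and largely not regression-based.** The operational model comes from comparing practices with the theoretical framework by mixed methods, and the acronym is expanded as a pilot observational study. This stands for the qualitative conclusions. It does not protect a p-value attached to a subtype.
- **The limitation is already disclosed.** It is, but as a matter of feasibility, without its consequence for the tests or the claims.

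A reader might infer that subtype, size, status and region are all nearly inseparable from one another, and that every association with organisational context fails. The documents do not support this: size + status and status + region are full rank, and the nurse-level scores are unaffected.

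**Conclusion.** The point holds for target subtypes. Five of seven are each identical with one centre, and in a model with size, status and region no subtype contrast is estimable (rank 10 of 16). This follows from Table 1 and needs no assumption beyond treating the target subtype as a centre-level factor.

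For size, status and region the problem is precision more than aliasing. Some of their joint models can be fitted, but each factor varies only between ten centres, and tests on respondents would overstate the information available.

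The false-positive rate depends on assumptions. With 5 patients per target nurse it is about 8% to 12% for an intraclass correlation of 0.05 to 0.10. A reader might take 17% to 27% as the headline; those figures need all of a centre's nurses to share its target subtype, which the article does not state. Nor does the evidence justify ruling out all models for size and status, or discounting the qualitative and framework-comparison conclusions.

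**What to change.** **In Analysis:**
1. Report contrasts between target subtypes descriptively, by centre, without p-values.
2. Treat any analysis of size, status or region as exploratory, with the centre as the unit.
3. For factors that vary within centres (perceived organisational support, role tension, patient deprivation and stage), include a centre term, fixed or random as the sample allows.

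**In Population or Table 1:** tabulate the non-target nurse types by centre, to show whether any subtype contrast can be made within centres.

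**In the Abstract's Discussion, Expected results and Justification of study population:** state that quantitative conclusions on subtypes describe them as implemented in these centres. The qualitative and framework-comparison conclusions need no change.

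**Cost.** The change is to wording plus one table, and the article says data collection was still under way. No inferential claim on subtype remains. Centre fixed effects would use 9 degrees of freedom on 38 nurses (3.8 per centre on average), which is fragile for logistic models; a random centre term may be the practical choice there.
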